#### • Oral health instructions (OHI)

After periodontal treatment, subjects will receive oral health instructions from the dentist that performed the scaling and root planing. These instructions will be given at V2 and V3 for the treatment group and at V5 and V6 for the control group. A 15-minute oral session will include verbal and visual information on how to use toothbrush, floss and interspace brushes, how to clean bridges and dentures, how and why to use a plaque disclosing test and a mouthwash.

A pack containing all the dental care products necessary for 3-months of periodontal maintenance will be given to the subjects at V2 for the treatment group and V5 for the control group. It will include three 75 ml tubes of toothpaste, three soft toothbrushes, 12 single-tufted interspace brushes, and sufficient dental floss and plaque disclosing tablets for a daily use over 3 months. An antiseptic mouthwash (chlorhexidine 0.12%) will also be given for mouth washing three times a day for 10 days after the scaling and root planing session.

Finally, the pack will contain leaflets that will provide pictorial information relative to the method, the frequency and the duration of each procedure.

Subjects in the control group will receive neither periodontal treatment nor a placebo during the 3-months follow-up (from V1 to V4). They will receive the same periodontal treatment as subjects in the treatment group (non-surgical scaling and root planing, systemic antibiotherapy, two-sessions of oral health instructions and antiseptic prescription) at V5 and V6 (Figure 1).

### Outcomes

#### HbA1c

The primary outcome of the DIAPERIO trial will be the difference in change of HbA1c from V1 to V4 between the two groups. The HbA1c level is proportional to average blood glucose concentration over the previous 1 to 3 months.

#### Fructosamine

A secondary outcome will be the difference in change of fructosamine levels from V1 to V3 and from V1 to V4 between the two groups. Fructosamine reflects an average of blood glucose levels over a period of 2 to 3 weeks.

#### Quality of life

A pragmatic outcome will be the difference in change in the quality of life between the two groups from V1 to V4. Quality of life will be assessed using the SF-36 questionnaire.

### Study assessments

#### Periodontal status

A full-mouth periodontal examination will be performed by trained dentists-examiners at V1 and V4 for both groups. The clinical examination will include depth of periodontal pockets (PPD in mm), level of clinical attachment (CAL in mm) and bleeding on probing (BOP: yes/no). Values will be taken for all scorable teeth at six sites per tooth (mesio-buccal, mid-buccal, disto-buccal, mesio-lingual, mid-lingual and disto-lingual). No radiographs will be taken. The result of the periodontal treatment will be assessed on the healing response in the tissues using PPD, CAL, BOP, and the amount of inflamed periodontal tissue (PISA)[14].

#### Questionnaires

At V1 and at V4, subjects will complete a questionnaire designed to gauge medical, social and oral health behavioral information. The questionnaire completed at V4 will assess the evolution of oral health behavior during the 3-months follow-up. Adverse events will also be reported. Reportable adverse events will include unexpected study-related events (oral adverse events) and serious adverse events regardless of cause.

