#### • Systemic antibiotherapy (ATB)

The French health authorities recommend the prescription of systemic antibiotherapy for metabolically unbalanced diabetic patients receiving periodontal treatment [12,13]. On primary intention, capsules of 500 mg amoxicillin will be prescribed to patients 3 times a day (morning, midday and evening) for 7 days. Two boxes of 12 capsules will be given to the patients after scaling and root planing (at V2 for the treatment group and at V5 for the control group). In case of contraindication to beta-lactam antibiotics, capsules of 300 mg clindamycin will be prescribed to patients twice a day (morning and evening) for 7 days. One box of 16 capsules will be given to the patients after scaling and root planing (at V2 for the treatment group and at V5 for the control group). These antibiotics are recommended by French health authorities for the treatment of chronic periodontitis in diabetic patients [13].

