For secondary outcomes, all continuous variables will be analysed via analysis of covariance using a model similar to that specified for the primary outcome. Analyses of binary variables will be based on logistic regression models adjusted for group and clinical centre. For secondary analyses, missing values will be imputed using the Last Observation Carried Forward method. The safety and efficacy of periodontal treatment will be assessed [17], as will the correlation between clinical response to periodontal treatment and HbA1c levels [18]. The proportion of subjects who had one or more adverse events in the two groups will be compared by means of Fisher's exact test.

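### The only adverse-event definition given does not fit an intervention with systemic antibiotics, or the between-group test of subjects with any adverse event

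*Protocol article*

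**What the plan says.** Under Study assessments, Questionnaires, the article says in general terms that adverse events are reported, and then specifies: "Reportable adverse events will include unexpected study-related events (oral adverse events) and serious adverse events regardless of cause". It gives no other definition.

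Under Systemic antibiotherapy (ATB), the first-line prescription is "capsules of 500 mg amoxicillin will be prescribed to patients 3 times a day (morning, midday and evening) for 7 days". For patients who cannot take beta-lactams it is "capsules of 300 mg clindamycin will be prescribed to patients twice a day (morning and evening) for 7 days". Both belong to the study intervention, together with scaling and root planing, chlorhexidine and oral health instructions. The section on oral health instructions states that controls have no periodontal treatment and no placebo between V1 and V4; they receive the same package from V5.

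Under Statistical methods, "The safety and efficacy of periodontal treatment will be assessed", and "The proportion of subjects who had one or more adverse events in the two groups will be compared by means of Fisher's exact test".

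**The concern.** Part of the intervention acts systemically, but the stated class of non-serious reportable events is oral. A non-serious event qualifies only if it is both unexpected and study-related, and the parenthesis equates that class with oral events. Two kinds of treatment effect then fall outside the definition: non-serious systemic reactions to the antibiotic, and expected oral effects of scaling or chlorhexidine.

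Before V4 these effects can arise from study treatment only in the treated arm. If they are not counted, the Fisher comparison loses part of the excess that it is meant to show. The article expects its results to support recommendations for clinicians and health policy, and these need a fair account of non-serious harm as well as of benefit. Events that are not recorded during follow-up can hardly be recovered later.

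**Working it through.** **Figures in the plan.** The article states no adverse-event rate and no power for the safety test, so there is no safety figure to reproduce. The one design figure used here is the target of 150 at 1:1 allocation, which gives 150 / 2 = 75 per arm. That target is sound: for a difference of 0.5, SD 1.0 and a two-sided 5% t-test, n = 63.8, so 64 per group (power 80.1%), and 128 / 0.85 = 150.6 against the stated 150.

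**Which events qualify under the stated definition.**

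| Event | Counted? | Reason |
|---|---|---|
| Serious, any cause | Yes | Explicitly included |
| Non-serious, oral, unexpected, study-related | Yes | Explicitly included |
| Non-serious, oral, expected effect of treatment | No | Not unexpected |
| Non-serious, systemic, antibiotic-related | No | Not oral |

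The events in the last two rows, when caused by study treatment, can occur only in the treated arm before V4.

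**Simple range (assumed rates).** Let a proportion *r* of treated patients have a non-serious antibiotic reaction. Patients concerned = 75 × *r*:
- *r* = 5%: 75 × 0.05 = 3.75, about 4
- *r* = 20%: 75 × 0.20 = 15

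**Effect on the Fisher test (illustration; every rate is assumed).** Let 5% of each arm have an event that the definition counts (75 × 0.05 = 3.75 subjects). Let a further proportion *x* of treated patients, independently, have a reaction that it does not count, with no uncounted events in controls. The treated-arm proportion with any event is then 1 − 0.95 × (1 − *x*). Power comes from exact enumeration, two-sided 5%, 75 per arm.

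| *x* | Any event, treated | Expected subjects | Not counted | Power, all events | Rejection rate, stated definition |
|---|---|---|---|---|---|
| 5% | 9.75% | 7.3 | 3.6 | 12% | 1.5% |
| 10% | 14.5% | 10.9 | 7.1 | 41% | 1.5% |
| 20% | 24.0% | 18.0 | 14.25 | 91% | 1.5% |
| 30% | 33.5% | 25.1 | 21.4 | >99% | 1.5% |

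The not-counted column is smaller than 75 × *x* because some patients also have a counted event. Under the stated definition both arms show 5% whatever *x* is, so the test cannot respond to the antibiotic reactions. Everyday complaints in both arms would lower the power in the all-events column; the illustration leaves them out.

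**The case against.** The strongest objection concerns wording. The definition says what reportable events *include*, not what they are limited to. *Reportable* may mean events to be notified and not everything recorded. The test sentence speaks of adverse events without the word reportable. The article also condenses a full protocol that is not shown and may define wider capture. This stands: a reader might infer that the trial is certain to undercount harm, and the text does not establish that. What remains is that the article does state a definition, offers no other for the test, and that definition does not match the intervention.

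It is also fair that serious reactions are captured in both arms regardless of cause, that safety is not among the listed objectives or outcomes, and that the HbA1c analysis is untouched.

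Three further inferences are tempting but not supported:
- *Adverse events rest on a 13-week recall.* They are described under the Questionnaires heading, but nothing says that they are collected only there or only at V4.
- *Controls yield no safety data after V5.* The article is silent on this, and controls do attend V5 and V6.
- *The relatedness criterion flatters the treatment.* In an open-label trial with untreated controls, that criterion by itself would tend to remove control-arm events and so widen the contrast. It works against the direction described here, and the net effect of the whole definition cannot be derived from the article.

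**Conclusion.** The point holds as a mismatch between a stated definition, the intervention and the planned test. It depends on one condition: that the definition under Questionnaires is the numerator of the Fisher test. On that condition, non-serious systemic reactions and expected oral effects of treatment are left out, and their omission pulls the comparison toward no difference.

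Only the direction of that omission follows from the article. The range of about 4 to 15 of 75 treated patients rests on an assumed rate of 5% to 20%, and the power figures rest on further assumed rates. No figure in the plan is wrong. The change is a cheap improvement worth making before enrolment; the validity of the primary result does not depend on it.

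**What to change.** - Replace the definition under Questionnaires with all adverse events: oral or systemic, expected or not, related or not. Classify each by seriousness and relatedness afterwards.
- Ask for them in the same way in both arms at V3 and V4, which both arms already attend.
- In Statistical methods, say that the Fisher test uses all adverse events from V1 to V4, so that it compares treated with untreated patients. Report oral and systemic events separately as well.
- Put any control-arm events after V5 in a separate descriptive table, because by then the controls have had the same treatment.

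**Cost.** One short form at visits that already exist, and a longer table. The safety profile may look less favourable. Counting unrelated events also adds everyday complaints in both arms, which is a further reason for the separate tables. If the full protocol already captures all events, one sentence saying which events enter the test is enough.

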### Randomization

Randomization will be blocked by centre. Subjects meeting eligibility criteria at V1 will be randomly assigned to receive periodontal treatment within 10 days (treatment group) or delayed periodontal treatment (control group) with the use of a block stratified according to clinical centre.

### Study timelines

The DIAPERIO trial will include 4 phases: pre-inclusion, inclusion-randomization, follow-up and post-follow-up (Figure 1). Maximum study length per participant will be 30 weeks. No longer term follow-up is planned. Table 1 shows the study schedule. V2 only concerns subjects from the treatment group, while V5 and V6 only concern subjects from the control group (delayed treatment).

**Table 1 T1:** Study schedule.

	V0	V1	V2	V3	V4	V5	V6
**Treatment group**							

Review of pre-inclusion criteria	*						

Review of inclusion criteria		*					

Written informed consent		*					

Full periodontal assessment		*			*		

Initial questionnaire + SF-36		*					

Blood collection (HbA1c)		*			*		

Blood collection (fructosamine)		*		*	*		

Periodontal treatment (SRP)			*				

Oral hygiene instructions			*	*			

Final questionnaire + SF-36					*		

Appointment for a next visit	*	*	*	*			

**Control group**							

Review of pre-inclusion criteria	*						

Review of inclusion criteria		*					

Written informed consent		*					

Full periodontal assessment		*			*		

Initial questionnaire + SF-36		*					

Blood collection (HbA1c)		*			*		

Blood collection (fructosamine)		*		*	*		

Periodontal treatment (SRP)						*	

Oral hygiene instructions						*	*

Final questionnaire + SF-36					*		

Appointment for a next visit	*	*		*	*	*	

### Statistical methods

Sample size calculation was based on detecting a difference of 0.5% in HbA1c change from baseline between the two groups. Assuming a standard deviation of 1.0% and using a 2-sided test at 5% significance level, 64 participants per group would yield 80% power. Anticipating a 15% dropout rate, the target sample size was thus planned at 150 participants.

Baseline characteristics by group will be presented as mean (SD) for continuous variables and tallied for categorical variables. The intention-to-treat population will consist of all randomized subjects whereas the evaluable population will consist of subjects from the intention-to-treat population who complete the 3-months follow-up. Descriptive statistics will be provided for the intention-to-treat population.

All primary analyses will be performed according to intention-to-treat principles, on the evaluable population (i.e. all patients with initial (V1) and final (V4) HbA1c measurements), regardless of the subject's presence at intermediate visits or his/her degree of compliance with the treatment. Subjects with missing initial or final HbA1c measurements will be excluded from the analysis. The main analysis will be a comparison between the two study groups concerning the change in the HbA1c levels from baseline to 3 months in an analysis of covariance (ANCOVA) model, adjusted for the baseline HbA1c level and clinical centre. Residual values will be examined for an approximate normal distribution. If HbA1c values are highly skewed, a transformation or non-parametric method will be used instead [15].

The data will also be analysed using the "per protocol" approach. Here the analysis will be restricted to participants who were compliant with the treatment protocol (SRP, ATB and OHI).

In addition to the primary analysis, five binary outcomes for HbA1c at 3 months (a relative decrease of ≥10%, a three-month level of < 7%, an absolute decrease of ≥0.5%, a relative increase of ≥10% and an absolute increase of ≥0.5%) will be evaluated in logistic regression models adjusted for the baseline HbA1c level and clinical centre [16].

For secondary outcomes, all continuous variables will be analysed via analysis of covariance using a model similar to that specified for the primary outcome. Analyses of binary variables will be based on logistic regression models adjusted for group and clinical centre. For secondary analyses, missing values will be imputed using the Last Observation Carried Forward method. The safety and efficacy of periodontal treatment will be assessed [17], as will the correlation between clinical response to periodontal treatment and HbA1c levels [18]. The proportion of subjects who had one or more adverse events in the two groups will be compared by means of Fisher's exact test.

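### The primary HbA1c analysis is labelled intention-to-treat but is, by the plan's own definition, a complete-case analysis, and no stated analysis of HbA1c change keeps all randomised patients

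*Protocol article*

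**What the plan says.** All of the following is in the protocol article, under Statistical methods unless stated otherwise.

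- ITT population: "The intention-to-treat population will consist of all randomized subjects".
- Evaluable population, as first introduced: "the evaluable population will consist of subjects from the intention-to-treat population who complete the 3-months follow-up".
- Primary analysis: "All primary analyses will be performed according to intention-to-treat principles, on the evaluable population". A parenthesis then restates evaluable as having HbA1c at both V1 and V4, and adds that attendance at intermediate visits and compliance do not matter.
- Missing data for the primary outcome: "Subjects with missing initial or final HbA1c measurements will be excluded from the analysis".
- The only task given to the full ITT population is descriptive statistics.
- A per-protocol analysis is also planned, on a set narrowed further to compliant patients.
- Last observation carried forward (LOCF) is stated for secondary analyses only.

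Under Inclusion criteria (V1), an HbA1c of 7.0 to 9.5% at V1 is required for entry. Table 1 has HbA1c taken at V1 and V4 only, and fructosamine at V1, V3 and V4.

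**The concern.** The label and the rule disagree. A reader told that the main result is ITT will assume that everyone randomised contributes to it. The stated rule instead removes each patient whose V4 HbA1c is missing, and 15% of patients are expected to drop out.

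Randomisation protects the comparison of all randomised patients. Once patients are removed for an event after randomisation, the comparison is unbiased only if the missing outcomes resemble the observed ones, given the covariates, or if the distortions in the two arms cancel. That assumption needs care here. Patients and dentists know the allocation. One arm is treated within 10 days, and the other gets no periodontal treatment until after V4. Reasons to return for V4 may therefore differ between arms. If loss is related to outcome and differs by arm, the HbA1c difference is biased, and no analysis described in the article would reveal it.

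**Working it through.** **Inputs from the article.** Target: "Sample size calculation was based on detecting a difference of 0.5% in HbA1c change from baseline between the two groups". Spread: "Assuming a standard deviation of 1.0" percentage points. Test: "using a 2-sided test at 5% significance level". Size: "64 participants per group would yield 80% power". Planned dropout is 15%, total 150, allocation 1:1 (75 per arm).

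**Assumed inputs, not in the article.** The gap g in HbA1c change between patients with and without a V4 value is taken as 0.5, 1.0 or 1.5 points. Planned dropout is split equally, 15% in each arm.

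**1. The plan's own figure.** For a two-sample t-test with difference 0.5, SD 1.0 and two-sided 5%, 80% power needs 63.77 per arm, that is 64. Power at 64 is 80.1%. Allowing for dropout, 128 / 0.85 = 150.6, against the stated 150. The figure reproduces.

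**2. Patients leaving the primary analysis.** 150 × 0.15 = 22.5, so 22 to 23 leave and about 127.5 (63.75 per arm) remain. Power at 63.75 per arm is 80.0%. The stated power therefore belongs to the complete-case set.

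**3. Bias.** With a share m missing in an arm, the mean over everyone randomised to that arm is (1 − m) × mean of observed + m × mean of missing. The complete-case mean is therefore off by m × g, and the between-arm bias is m_T × g_T − m_C × g_C.

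- Gap in one arm only, m = 0.15: 0.15 × 0.5 = 0.075 and 0.15 × 1.0 = 0.15.
- Relative to the target: 0.075 / 0.5 = 15% and 0.15 / 0.5 = 30%.
- Same m and same g in both arms: the terms cancel and the bias is zero.

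**4. What that bias does to the test.** The complete-case standard error is 1.0 × √(2 / 63.75) = 0.177. Suppose there is no true effect, the missing treated patients did worse than treated completers by g, and control loss is random.

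| Assumed gap g | Bias | Two-sided type I error |
|---|---|---|
| 0.5 | 0.075 | about 7% |
| 1.0 | 0.15 | about 13% |
| 1.5 | 0.225 | about 24% |

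**5. Tipping point.** The smallest significant difference at 63.75 per arm is about 0.35. An observed 0.50 loses significance when 0.15 × g exceeds 0.50 − 0.35 = 0.15, so g is about 1.0. With the standard error for 75 per arm, the threshold is about 0.32 and g is about 1.2.

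**6. Would LOCF help?** HbA1c has no measurement between V1 and V4. Carrying the last value forward would enter V1 again, which is a change of exactly zero.

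**The case against.** The best defence is that the sentence containing the ITT label also names the evaluable set, so the exclusion is disclosed, and that the sample size was inflated to leave about 64 per arm in that set. This is true. It shows that the rule was deliberate, but it does not make the label right under the article's own definition of ITT.

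Several stronger readings are tempting and not supported.

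- *The two definitions of evaluable leave the primary set undetermined.* They do not. The wordings differ: someone attending V4 without a valid HbA1c could meet the first and not the second. But the parenthesis and the exclusion sentence make V1 plus V4 HbA1c the operative rule.
- *It is an analysis of treatment completers.* It is not. Non-compliers and those who miss intermediate visits stay in if V4 HbA1c exists.
- *Excluding a missing initial HbA1c contradicts the entry criteria.* It is merely redundant, because V1 HbA1c is needed for entry.
- *Nothing at all guards against informative loss.* The article is condensed, and an unseen analysis plan may add sensitivity analyses. The point stands on what the article states: a label and a rule that disagree.
- *The LOCF statement covers this.* The five additional binary HbA1c outcomes might arguably fall under it and so retain patients without V4. That still gives no all-randomised analysis of mean change, and it would assume zero change.
- *Controls will be the ones lost.* The direction is unknown. Controls have free treatment due at V5, which is a reason to attend V4. A control who seeks care elsewhere but attends V4 is contaminated, not missing.

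It is also fair that the assumed gaps are large, at half to one and a half times the planning SD, and that a bias of 0.15 is smaller than the standard error of 0.177. Those figures show sensitivity. They are not forecasts.

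**Conclusion.** The point holds in this form: the main result is a complete-case analysis as randomised, carrying an ITT label that the article's own definition does not support, and the article states no analysis of HbA1c change that keeps all randomised patients. About 22 to 23 of 150 patients are affected at the planned dropout; this figure rests only on the article's numbers. The bias of 0.075 to 0.15 points depends on assumed loss and an assumed gap in one arm, and may be zero or of either sign. The loose wording of the evaluable set is a minor matter. A reader might infer a sample size error, but there is none: 64 per arm and 150 in total are consistent with the set that is analysed.

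**What to change.** Settle the following before any HbA1c outcome is examined by arm.

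1. Define the evaluable set once, as randomised patients with V1 and V4 HbA1c, and call it complete case or modified ITT.
2. Prespecify the same ANCOVA on all randomised patients, analysed as randomised, with multiple imputation of missing V4 HbA1c from arm, centre, baseline HbA1c and V1 and V3 fructosamine. These variables are already collected.
3. Add a delta-adjusted (tipping-point) sensitivity analysis, varied separately by arm. On the figures above, the range should reach beyond 1.0 to 1.2 points.

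The cost is a paragraph of wording and a little more analysis, with no extra visits. The all-randomised estimate may be slightly less favourable. If missing treated patients are assumed to gain no benefit, the difference falls to 0.85 × 0.5 = 0.425, and power with 75 per arm is 73.4%; 80% would need 88 per arm. That figure treats all 75 outcomes as observed, so it is generous for imputed data. It is a reason to read the new analyses as support for the complete-case result, not a reason to resize the trial.

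Retrieving routine HbA1c values for patients without V4 is optional. The article uses routine values only for pre-screening (Pre-inclusion criteria (V0)) and does not show that one would exist near week 13, so the fix should not depend on it.

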## Methods

The DIAPERIO trial is an open-label, 13-week follow-up, randomized, controlled trial. The design specifies a balanced (1:1) treatment allocation.

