##### Pre-inclusion criteria (V0)

To be pre-included, patients will have to:

- be aged 18 years or older (male or female),

- be affiliated to a public health system,

- be diagnosed as having had type 1 or 2 diabetes for at least one year before V0,

- have a last known value of HbA1c, measured within three months prior V0, between 6.8% and 9.7%,

- have received stable antidiabetic therapy (no changes to diet, medication, dosage or formulation) during the three months preceding V0,

- have at least six natural permanent teeth,

- be available for all study visits over three months in the Dental Care Departments (V1 to V6),

- be able to give their written informed consent.

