##### Inclusion criteria (V1)

Final inclusion will be decided at the Dental Care Departments, during the inclusion visit (V1). The criteria for inclusion are:

- written informed consent,

- no change relative to pre-inclusion criteria and non-inclusion criteria since V0,

- patient with periodontitis. Periodontitis is defined by the presence of one site with periodontal probing depth (PPD) ≥ 4 millimetres and clinical attachment level (CAL) ≥ 3 millimetres on at least 4 teeth.

- patient with HbA1c level ≥ 7.0% and ≤ 9.5%. Blood samples will be taken during V1, after periodontal assessment. Thus blood will only be taken from patients with periodontitis.

Subjects fulfilling all the inclusion criteria and none of the non-inclusion criteria at V1 will be randomized and will be given a scheduled appointment at the Dental Care Department, within 10 days for the treatment group (V2), and between 21 and 31 days from V1 for the control group (V3) (Figure 1).

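### Diabetes type could be added cheaply to the primary ANCOVA of a trial that mixes type 1 and type 2 patients; this is an improvement, not a correction of an error

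*Protocol article*

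**What the plan says.** The pre-inclusion criteria of the protocol article admit both forms of the disease: patients must "be diagnosed as having had type 1 or 2 diabetes for at least one year before V0". Under Randomization, allocation is made "with the use of a block stratified according to clinical centre", and no other stratum is named. Under Statistical methods, the change in HbA1c is compared "in an analysis of covariance (ANCOVA) model, adjusted for the baseline HbA1c level and clinical centre". The five binary HbA1c outcomes "will be evaluated in logistic regression models adjusted for the baseline HbA1c level and clinical centre". Continuous secondary outcomes are to follow a model similar to the primary one. Diabetes type appears in none of these.

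Two other provisions bear on the point. Entry HbA1c is confined to 7.0-9.5%, and patients must "have received stable antidiabetic therapy (no changes to diet, medication, dosage or formulation) during the three months preceding V0". The inclusion visit (V1) then requires that nothing in those criteria has changed since V0. The article states no corresponding requirement for V1 to V4, the interval over which the primary outcome is measured.

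**The concern.** Type 1 and type 2 diabetes differ in disease process and in how treatment is adjusted, so the mean 13-week change in HbA1c could plausibly differ between them even at the same baseline value. Adjusting for baseline HbA1c does not remove a difference in course, and the therapy rule stated in the article covers the time before enrolment, not the follow-up.

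If type does predict change, two things follow. Its contribution stays in the residual and costs some precision. And if the arms differ by chance in their share of type 1 patients, the estimate moves with that difference. The imbalance would show in the planned baseline table of an open-label trial, where adding the covariate after the fact is hard to defend. Naming it beforehand avoids that.

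The covariate set is stated explicitly in the article, so this concerns a stated choice, not a detail left to an analysis plan.

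**Working it through.** **The plan's own figure.** The sample size is based on "detecting a difference of 0.5% in HbA1c change from baseline between the two groups", with SD 1.0, two-sided 5%, 80% power, 64 per group and 15% dropout.
- The normal approximation gives 63 per group. The noncentral t gives 79.5% power at 63 and 80.1% at 64, so 64 is right.
- Dropout: 128 / 0.85 = 150.6, against a stated total of 150.
- With 64 per arm, SE = 1.0 × √(2/64) = 0.177, and power by normal approximation is 80.7%. This is the reference below.

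**Assumptions, not in the protocol.**
- Type 1 share p = 0.2 to 0.4.
- Difference between types in mean HbA1c change, after adjustment for baseline and centre, g = 0.2 to 0.5 points.
- 64 evaluable patients per arm, residual SD 1.0 before type is added, and type left to chance.

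**Chance imbalance.** SD of the difference in type 1 share = √(2p(1−p)/64). The shift in the treatment estimate is the imbalance times g.

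| p | SD of difference | 1.96 SD | Shift, g = 0.2 | Shift, g = 0.5 | Probability of a gap ≥ 10 points |
|---|---|---|---|---|---|
| 0.2 | 0.071 | 0.139 | 0.028 | 0.069 | 15% |
| 0.3 | 0.081 | 0.159 | 0.032 | 0.079 | 21% |
| 0.4 | 0.087 | 0.170 | 0.034 | 0.085 | 24% |

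These shifts are tail values. Relative to the SE they run from 0.028/0.177 = 0.16 to 0.085/0.177 = 0.48. A typical (1 SD) shift is 0.071 × 0.2 = 0.014 to 0.087 × 0.5 = 0.043 points.

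**Precision.** Type explains a variance of p(1−p)g². The residual SD becomes √(1 − p(1−p)g²).
- p = 0.2, g = 0.2: 0.16 × 0.04 = 0.0064; SD 0.997; power 81.0%.
- p = 0.2, g = 0.5: 0.16 × 0.25 = 0.040; SD 0.980; power 82.3%.
- p = 0.4, g = 0.2: 0.24 × 0.04 = 0.0096; SD 0.995; power 81.1%.
- p = 0.4, g = 0.5: 0.24 × 0.25 = 0.060; SD 0.970; power 83.1%.

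**Cost if type predicts nothing.** The current model has four parameters (intercept, group, baseline, one centre contrast), leaving 128 − 4 = 124 residual degrees of freedom. An extra, useless covariate inflates the variance of the treatment effect on average by about 1/124 = 0.8%, through its chance correlation with group. That costs about 0.3 points of power; the lost degree of freedom itself is negligible.

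**Break-even.** Gain and cost cancel when p(1−p)g² is about 0.008. That is g = √(0.008/0.16) = 0.22 at p = 0.2, and √(0.008/0.24) = 0.18 at p = 0.4. At the low end of the assumed range adjustment is therefore about neutral for power. At the high end it gains about 2 points net.

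**The case against.** The strongest reply is that nothing here is wrong. The model is fixed in advance and contains the outcome's baseline value and the stratification factor, which is a standard and defensible choice. Chance imbalance under randomisation is not bias: its contribution is already in the residual variance, the SE and the test. All of this stands.

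The premise is also undocumented. A reader might infer that diabetes type is an established determinant of the outcome here. The article nowhere says so, and what matters is whether type predicts change once baseline HbA1c and centre are in the model. The narrow entry range and the stable-therapy rule before entry already limit differences between types. Therapy changes after V1 are possible, but no passage says that they differ by type. The same case could be made for other baseline characteristics. Type is only the plainest split written into the eligibility criteria, and it is recorded for everyone.

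A reader might also infer that adjustment can only help precision. It cannot be guaranteed to: if type is not prognostic it costs a little. In the logistic models, adding a prognostic covariate changes the odds ratio being estimated and generally widens the standard error of its logarithm. This is why those models are left alone.

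What survives is that the expected loss from adding the term is very small, the possible gain is modest, and the choice can be made cleanly only beforehand. Subgroup or sensitivity analyses by type may be in the full protocol or analysis plan, which are not shown, and their absence from the article is not held against it.

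**Conclusion.** A low-cost improvement, not an error or a contradiction. It would be tempting to read the omission as a source of bias, or as a threat to the primary test or the sample size. The documents support none of these: "The design specifies a balanced (1:1) treatment allocation", the two-sided 5% test is valid without type, and the stated 64 per group and 150 in total reproduce.

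Under the assumed ranges (20-40% type 1, a between-type difference of 0.2-0.5 points, 64 evaluable patients per arm), a 1.96-SD imbalance moves the estimate by about 0.03-0.085 HbA1c points. That is 6-17% of the 0.5-point target (0.03/0.5 to 0.085/0.5) and at most about half a standard error. Average power rises from about 80.7% to 81-83%, less about 0.3 points for the extra term. The case depends on the between-type difference being nearer 0.5 than 0.2, which the article does not settle.

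**What to change.** Prespecify diabetes type (1 vs 2) as a fixed covariate, beside baseline HbA1c and clinical centre, in the primary ANCOVA and in the similar ANCOVA models for continuous secondary outcomes. Leave the randomisation strata and the logistic models unchanged. The change must be made before outcome data are examined.

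The cost is one model term and one degree of freedom, or about 0.3 points of power if type turns out not to be prognostic. No new data are needed, since type is established at V0, and the change remains possible even if the randomisation lists have been issued. The planned sample size need not change.
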